### Intervention

2.4

The intervention period will last for 14 days. All participants will receive routine rehabilitation care, as shown in Table 1. These treatments adhere to local relevant guidelines (15, 16). Swallowing rehabilitation interventions will be arranged based on the Chinese Dysphagia Rehabilitation Management and Guidelines (Appendix S2) (17). There are no intergroup differences in the rehabilitation care across the trial site hospitals.

**Table 1 tab1:** A summary of the core standardized components, structure, and implementation of the intervention.

Intervention	Description	Timepoint and frequency
Risk factor control	Interventions are implemented for stroke-related risk factors, including blood pressure, blood lipid levels, blood glucose levels, tobacco and alcohol consumption, and physical activity. These interventions encompass lifestyle modifications (e.g., smoking and alcohol cessation, dietary adjustments) and pharmacological interventions (e.g., hypoglycemic agents, antihypertensive drugs).	Routine
Stroke recurrence prevention	Stroke recurrence prevention is a systematic intervention strategy aimed at reducing the risk of recurrent cerebrovascular events in patients with a history of stroke. Beyond risk factor control, pharmacological therapy is administered based on the etiological subtypes of stroke, such as aspirin, statins, and anticoagulants.	Routine
Health education	Health education is a critical component of stroke recurrence prevention that bridges the gap between clinical interventions and patient adherence, ensuring that patients and their caregivers fully understand and implement secondary prevention measures. It includes (1) Disease Knowledge Education, (2) Medication and Rehabilitation Compliance Education, (3) Lifestyle Intervention Guidance, (4) and (5) Psychological Adjustment Guidance	Day 1
Swallowing rehabilitation	All patients receive identical daily swallowing behavior rehabilitation (30–40 min/session, 6 days/week), including oral motor training, pharyngeal facilitation, swallowing maneuvers, and secretion management.	Monday to Saturday morning
Oral hygiene	Mouthwash and dental cleaning tools are used to help patients clean their oral cavity.	Every morning

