### Outcomes

2.5

Several assessment timepoints are defined as follows: baseline (T0), after the intervention period ends at day 15 (T1), and follow-up at day 43 (T2). The SPIRIT participant timeline is shown in Figure 2 (10).

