#### Secondary outcomes

2.5.2

Based on the FEES at T0 and T1, (1) the Murray Secretion Scale (MSS), (2) the Yale Pharyngeal Residual Severity Rating Scale (YPR-SRS), and the Penetration-Aspiration Scale (PAS) will be used to assess the accumulation of secretions, pharyngeal residue after swallowing, and airway protection (26–28). The MSS, YPR-SRS, and PAS are ordinal four-, five-, and eight-level scales, respectively, with higher grades indicating more severe conditions. The MSS, YPR-SRS, and PAS are assessor-blinded. (4) The time to improvement of one level from the baseline DOSS will be recorded (14). A one-level increase in the DOSS is considered clinically significant as it indicates reduced need for non-oral feeding, lower risk of aspiration and pneumonia, earlier transition to oral intake, and improved functional independence. However, it is apparently impractical to conduct daily instrumental swallowing assessments. Therefore, a three-step decision-making strategy is designed to determine clinical improvement. First, researchers will conduct preliminary evaluations by observing the participants’ daily conditions, feeding, and swallowing training performance. Participants identified as having the potential for a one-level improvement will undergo a swallowing screen, which will be compared with the baseline results for definitive evaluations. Then, detailed communication will be conducted to obtain participants’ perception of the swallowing condition. Subsequently, researchers will decide whether to conduct an additional FEES to verify the degree of the DOSS improvement. This design is intended to minimize intra-individual heterogeneity in swallowing assessments and to incorporate patient performance, patient perceptions, caregiver observations, and instrumental assessments, with details shown in Appendix S3. (5) Time to oral intake will be recorded, defined as the first day, during the two-week intervention period, on which a participant meets level 3 or above on the Dysphagia Outcome and Severity Scale. (6) Aspiration symptoms will be monitored for 6 weeks. Participants will be instructed to record daily on a paper or electronic calendar the occurrence of overt aspiration, the materials causing the aspiration, and whether the aspiration is resolved. Overt aspiration is defined as coughing or discomfort triggered by the aspiration of food or water into the airway (29). Resolution of aspiration is defined as the disappearance of discomfort with behavioral steps, such as coughing or back patting. To address potential recall bias and underreporting of aspiration, some measures are taken, as shown in Appendix S4. To monitor silent aspiration, new-onset aspiration pneumonia will be tracked over a 6-week period (Appendix S4). After discharge, this study will accept aspiration pneumonia diagnosed by qualified physicians at any tertiary hospital, as long as the primary diagnosis is coded as ICD-10 J69.0 or the patient is explicitly diagnosed with aspiration pneumonia (30). The time to improvement of one level from the baseline DOSS, time to oral intake, and aspiration symptoms are open-label assessments.

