### Sample size

2.7

Previous studies have lacked assessments using the gold standard. Therefore, we conducted a preliminary study to determine the sample size. In this study, 48 ischemic stroke patients were randomly assigned in a 1:1 ratio to the OE and NG groups, and their baseline and day 15 DOSS scores were assessed. The sample loss rate was conservatively set at 30%. Based on the results and Cohen’s formula, at least 211 participants were required for each group. The formula is as follows:

$$n1=n2=\frac{2\times {\left(Z_{\alpha {/}_{2}}+Z_{\beta }\right)}^{2}\times \sigma^{2}}{{\left(M1-M2\right)}^{2}}÷0.7$$

In this case, the corrected *α* = 0.007, (1−*β*) = 95%. M1 = 4.00, M2 = 5.16, 
σ
=2.39. The effect size was derived from our preliminary randomized trial using FEES-confirmed DOSS scores. Given the lack of prior large-scale rigorous data using gold-standard swallowing assessments, this effect size represents a clinically plausible and realistic improvement supported by our pilot data and clinical experience. This target sample size (n1 = n2 = 211) is higher than that found in related studies retrieved from common databases such as the Web of Science, PUBMED, and CNKI. Sample size calculations based on other parameters yielded results below this value. To ensure the test power, these results were not adopted. The sample sizes in other scenarios are shown in Appendix S5.

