### Statistical methods

2.9

Generalized Estimating Equations will be used to analyze repeated measures data, including the baseline and outcome DOSS, MSS, YPR-SRS, and PAS. The analyzed effects will include time, between-group, and interaction terms. Significant interaction effects indicate that differential interventions can impact the outcomes over time. Based on the primary outcome, additional analysis will be conducted by comparing the intergroup differences in the proportion of participants who will achieve oral intake at T1, using the chi-square test. The time to improvement of one level from the baseline DOSS and the time to oral intake will be analyzed using stratified log-rank tests, with stratification by the baseline DOSS. Data from patients who do not achieve their goals will be censored at day 42. The number of overt aspiration per person over 6 weeks will be analyzed using negative binomial regression to assess intergroup differences in incidence rates. Kaplan–Meier analysis will be used to handle the occurrence of aspiration pneumonia and to plot survival function curves. Statistical analyses will be based on intention-to-treat, and multiple imputation methods will be used to address partial missing values (31). Furthermore, we plan to perform several sensitivity analyses, including per-protocol analysis using a sample that excludes dropouts, and exclusion of centers from different geographic regions, to explore the stability of the main findings. The significance level *α* has been adjusted to 0.007 based on the number of outcomes (Bonferroni). Statistical analyses will be conducted using Stata v18.0 MP.

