## Discussion

3

This study is important as it will rigorously and systematically investigate the effects of oro-esophageal versus nasogastric feeding on swallowing outcomes. This study plans to include a broad sample of inpatients with ischemic stroke, focusing on both general and local swallowing function, and will track functional improvements throughout the intervention period rather than only assessing the baseline and post-intervention status. Our findings are expected to provide evidence-based support for clinical decision-making in enteral nutrition.

Gastrostomy is not widely accepted in East Asia because of its invasive nature. Oro-esophageal tube feeding offers an alternative to nasogastric feeding and is therefore worthy of investigation. Compared with nasogastric feeding, if proven to more effectively improve swallowing function, to be non-inferior in safety, and to help reduce overt aspiration or the risk of aspiration pneumonia, this will provide further support for the promotion of oro-esophageal tube feeding. This will benefit not only clinical practice but also patients’ rehabilitation outcomes and quality of life.

This study will adopt the DOSS as the primary outcome. The consideration for this choice is that the DOSS is a widely accepted, clinically intuitive ordinal scale directly associated with any decision about oral intake and tube weaning. It is routinely used in swallowing rehabilitation and aligned with real-world clinical decision-making.

It is rated based on the gold-standard instrument for dysphagia, ensuring objectivity and physiological grounding. Although the DOSS is ordinal, a one-level improvement over 14 days can represent a clinically significant shift in swallowing function in acute stroke rehabilitation. This change corresponds to reduced aspiration risk, better secretion control, earlier achievement of oral intake, and lower dependence on tube feeding. To address the limited granularity of an ordinal scale, we include the MSS, YPR-SRS, and PAS as secondary outcomes. These measures directly quantify physiological improvements in secretion pooling, pharyngeal residue, and airway protection, which may not be fully captured by DOSS alone. We further strengthen sensitivity by analyzing time to one-level DOSS improvement and time to oral intake, which can capture the speed and timing of recovery rather than only endpoint status.

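### Day-42 censoring of the two DOSS time-to-event outcomes does not match their 14–15 day observation window and, as written, counts early dropouts as followed failures

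*Protocol article*

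**What the plan says.** Statistical methods (2.9) assigns both DOSS time-to-event outcomes to one test: they "will be analyzed using stratified log-rank tests, with stratification by the baseline DOSS". The next sentence gives the censoring rule: "Data from patients who do not achieve their goals will be censored at day 42". It makes no exception for participants who leave early. The same section plans multiple imputation for partly missing values and a per-protocol sensitivity analysis without dropouts, but ties neither to censoring times.

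Secondary outcomes (2.5.2) sets the event window for time to oral intake: it is "defined as the first day, during the two-week intervention period, on which a participant meets level 3 or above" of the DOSS. Intervention (2.4) fixes that period: "The intervention period will last for 14 days". For time to one-level improvement, 2.5.2 states no end date, but the Discussion says the study "will track functional improvements throughout the intervention period rather than only assessing the baseline and post-intervention status". During treatment, FEES is not scheduled: after screening steps, "researchers will decide whether to conduct an additional FEES to verify the degree of the DOSS improvement".

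Outcomes (2.5) and Primary outcome (2.5.1) schedule DOSS at baseline and at T1 (day 15) only. T2 is day 43, and only the aspiration outcomes are followed for six weeks. On attrition, the Sample size section (2.7) says: "The sample loss rate was conservatively set at 30" percent.

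**The concern.** A censoring time states how long a participant was known to be event-free. Day 42 is 27 to 28 days after anyone's DOSS status was last observed, so the rule claims knowledge the trial will not have. It also covers a participant lost on day 3 without the event, who would stay in the risk set at every later event time as though watched and seen not to improve.

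Speed of improvement is a stated objective and the first evidence gap named in the Introduction, and these two outcomes are the ones that address it. If one arm loses more participants than the other, that arm will appear to recover more slowly for reasons unrelated to swallowing. Participants and interventionists are unblinded and the two tube methods differ visibly, so unequal loss is possible, though the article neither predicts nor quantifies it.

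A second inconsistency lies in the event window. The only scheduled post-baseline FEES is on day 15, one day after a 14-day period ends.

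**Working it through.** The plan gives no event rate, hazard ratio or power for these outcomes, so there is no figure of its own to reproduce. Taken from the article: 211 per arm, 1:1 allocation, two-sided alpha 0.007, log-rank test in two baseline DOSS strata, 30% loss. Assumed: event probabilities, the timing of loss and its split between arms.

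**1. The dates side by side**

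| Item | Window | Section |
|---|---|---|
| Time to oral intake | within the 14-day intervention | 2.5.2, 2.4 |
| Time to one-level improvement | no end date; tracking described as during the intervention | 2.5.2, Discussion |
| Last scheduled DOSS | day 15 | 2.5, 2.5.1 |
| Aspiration outcomes | 6 weeks | 2.5.2 |
| Censoring of both DOSS outcomes | day 42 | 2.9 |

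42 − 15 = 27 and 42 − 14 = 28 days without DOSS observation.

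**2. Completers without an event.** The log-rank numerator is Σ(d₁ⱼ − dⱼ·n₁ⱼ/nⱼ), summed over event times j. No event can be recorded after the window, so a completer is in the same risk sets whether censored at its end or at day 42. In simulation the two statistics were identical (maximum difference 0). With no dropout, rejection was 0.006 under both rules.

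**3. Equal loss.** Assume 60% improve by day 14 at a constant daily hazard, and 30% of each arm drops out, uniformly over days 1–14. The daily probability of not improving is q = 0.4^(1/14) = 0.9367. A dropout's average chance of improving before leaving is 1 − (1/14)Σq^u for u = 1 to 14, which is 1 − 8.87/14 = 0.366. Under the day-42 rule the apparent day-14 proportion is events divided by all randomised: 0.7 × 0.60 + 0.3 × 0.366 = 0.53, against a true 0.60.

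**4. Log-rank simulations.** Assume 50% true event probability by day 14, exponential event and dropout times, and 2,000 runs per scenario. The rejection rate at alpha 0.007 with no true difference was:

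| Dropout by arm | Day-42 rule | Last observation (at most day 14) |
|---|---|---|
| 30% / 30% | 0.006 | 0.009 |
| 25% / 35% | 0.015 | 0.006 |
| 10% / 30% | 0.044 | 0.010 |
| 20% / 40% | 0.049 | 0.008 |

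The Monte Carlo standard error at 0.007 is √(0.007 × 0.993/2000) = 0.002. As a check, the mean z under the day-42 rule was −0.53 at 25%/35% and −1.05 at 20%/40%. The critical value is 2.697, and the normal tails beyond 2.697 − 0.53 = 2.17 and 2.697 − 1.05 = 1.65 are 0.015 and 0.049.

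Under the step 3 model (60% events, uniform dropout, 3,000 runs), 20%/40% loss gave 0.034 to 0.036 in two separate runs, against 0.008 to 0.009 with censoring at dropout.

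Power with true event probabilities of 50% and 65%: 0.54 (day 42) against 0.60 (last observation) at 30%/30% loss, and 0.15 against 0.60 at 20%/40% when the better arm loses more.

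**5. The day-15 FEES.** Take a participant with no triggered FEES who is first found at level 3 on day 15. The T1 chi-square test in 2.9 counts this participant as having achieved oral intake. Under the 2.5.2 definition, day 15 falls outside a 14-day period, so the log-rank analysis can count the same participant as event-free to day 42. This follows from the event definition, not from the day-42 date.

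**The case against.** The date alone does not harm the test: step 2 shows that completers contribute identically. A reader might infer that day-42 censoring invalidates the log-rank test outright, or always understates improvement. The documents do not support that; with full follow-up only the plotted curve is affected. This part of the objection stands.

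It can also be said that the sentence concerns participants who fail to reach the goal, not those lost with unknown status, and that imputation, the per-protocol analysis or an unseen analysis plan would deal with dropouts. This stands only in part. The article states a specific rule, gives no exception and connects neither provision to censoring times. An analyst following it literally would censor a day-3 dropout at day 42.

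Nothing in the article suggests 20% versus 40% loss. The 30% is described as conservative, serves the sample size, and has no stated timing or split by arm. Participants expected to leave within two weeks are excluded. So the unequal-loss figures illustrate what the rule can do; they are not forecasts. With equal loss, type I error is kept.

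On day 15, a reader might infer that such improvements are certainly lost for both outcomes, or might put a percentage on that loss. Neither follows. The two-week limit is explicit only for oral intake, and Appendix S3 is not shown. The Abstract's 15 days of feeding and the wording of 2.5 allow day 15 to be read as the close of the window. Any percentage would need a daily detection rate that the article does not give.

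**Conclusion.** The censoring rule is wrong as written for the two DOSS time-to-event outcomes, because day 42 belongs to the aspiration follow-up. The conflict is explicit for time to oral intake. For one-level improvement it is inferred from the DOSS schedule and the Discussion.

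The effect depends entirely on loss before day 15:

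- No loss: the test is unchanged, and the curve extends over about four unobserved weeks.
- Equal loss: improvement is understated (53% for 60% at 30% loss) and power falls modestly (0.60 to 0.54).
- Unequal loss: the comparison is biased against the arm losing more participants. Type I error is about 0.015 at 25%/35% and 0.03–0.05 at 20%/40%, against 0.007.

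All these sizes rest on the assumed event rates and dropout patterns given in the working. The day-15 inconsistency between the log-rank and chi-square analyses is a separate matter of definition. For one-level improvement, the text does not say whether the day-15 FEES counts.

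This should be fixed, but it is not critical: two open-label secondary outcomes are affected, and the assessor-blinded primary DOSS analysis is not.

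**What to change.** In 2.9, for both DOSS time-to-event outcomes, censor participants without the event at the last day they were under in-trial observation for swallowing status, at latest day 15. Do not tie censoring to the last DOSS rating: FEES between baseline and day 15 happens only if triggered, so that rule would send most dropouts back to baseline.

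In 2.5.2, extend the oral-intake window to include T1, and state for both outcomes that a level first met on the day-15 FEES is an event at day 15. Completers without the event are then censored at day 15 as well, so that they are at risk when those events occur. This keeps the planned stratified log-rank test; interval-censored methods would not fit it.

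Keep day 42 for aspiration pneumonia only, with dropouts censored at last contact, and reconcile it with T2 at day 43.

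The cost is a few sentences in 2.5.2 and 2.9. No extra assessments or change in sample size are needed, but each participant's last day of observation must be recorded.

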**Outcomes:**

The primary outcome is the dysphagia severity assessed using the Dysphagia Outcome and Severity Scale (DOSS). The secondary outcomes include time to improvement of one level from the baseline DOSS, time to oral intake, accumulation of secretions assessed using the Murray Secretion Scale, pharyngeal residue after swallowing assessed using the Yale Pharyngeal Residual Severity Rating Scale, and airway protection assessed using the Penetration-Aspiration Scale. Aspiration symptoms will be monitored for 6 weeks.

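### The single primary outcome, DOSS, is tested at a flat Bonferroni level of 0.007: valid but needlessly conservative, and whether that level covers every listed comparison depends on how they are counted

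*Protocol article*

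**What the plan says.** The abstract states: "The primary outcome is the dysphagia severity assessed using the Dysphagia Outcome and Severity Scale (DOSS"). Section 2.5.1 and the Discussion name the same single primary outcome. Section 2.5.2 lists six numbered secondary items: MSS, YPR-SRS, PAS, time to a one-level DOSS improvement, time to oral intake, and aspiration symptoms.

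Section 2.9 sets one significance level for the whole trial, which "has been adjusted to 0.007 based on the number of outcomes (Bonferroni"). It gives no order of testing and no separate level for the primary. Section 2.7 confirms that the level applies to DOSS, because the sample size for DOSS uses "the corrected *α* = 0.007, (1−*β*) = 95"%, with "M1 = 4.00, M2 = 5.16" and an SD of 2.39.

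Section 2.9 assigns these methods:
- generalized estimating equations for DOSS, MSS, YPR-SRS and PAS;
- stratified log-rank tests for the two time-to-event outcomes;
- negative binomial regression for overt aspiration;
- for aspiration pneumonia, "Kaplan–Meier analysis will be used to handle the occurrence of aspiration pneumonia", with no test named;
- as an additional analysis based on the primary outcome, "comparing the intergroup differences in the proportion of participants who will achieve oral intake at T1, using the chi-square test".

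**The concern.** A Bonferroni correction across all outcomes treats them as equals. This plan does not: it names one primary outcome. When one primary hypothesis is tested first and the secondaries are opened only if it succeeds, the primary can be tested at the full 5% and the family-wise error stays at 5%. Under the plan as written, a DOSS result with p between 0.007 and 0.05 would be declared negative only because secondary outcomes exist. The planning effect comes from a pilot of 48 patients, so a true effect below 1.16 is a realistic possibility, and that is where the stricter level costs most.

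The second, smaller question is whether 0.007 covers everything section 2.9 compares. The numbered item for aspiration symptoms holds two endpoints with separate analyses, and the chi-square test comes on top.

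**Working it through.** **Inputs.** From section 2.7: two-sided α = 0.007 (the formula uses Z at α/2), power 95%, difference 5.16 − 4.00 = 1.16, SD 2.39, loss 30% applied as division by 0.7, and 211 per group. From section 2.9: the list of comparisons above. The divisor behind 0.007 is not stated. 0.05/7 = 0.00714 fits one primary plus six numbered secondary items.

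**The plan's own sample size.** n = 2 × (2.697 + 1.645)² × 2.39² / 1.16² = 160.04 evaluable per group, and 160.04/0.7 = 228.6, so 229 per group. The stated 211 does not follow from the printed formula. This is a separate matter, but it affects how the power figures below should be read. With 160.04 evaluable per group, power at 0.007 is 95.0%, as intended. With 211 randomised, 211 × 0.7 = 147.7 are evaluable.

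**Cost in patients.** The same formula at two-sided 0.05 gives n = 110.3 evaluable and 110.3/0.7 = 157.6, so 158 per group. On the plan's own inputs, the stricter level asks for 229 − 158 = 71 more patients per group.

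**Cost in power at the planned size.** Power = Φ(δ/SE − z), with SE = 2.39 × √(2/147.7) = 0.2781, z = 2.697 at 0.007 and z = 1.960 at 0.05.

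| Difference δ | δ/SE | Power at 0.007 | Power at 0.05 |
|---|---|---|---|
| 1.16 (plan) | 4.171 | 93.0% | 98.6% |
| 1.0 (assumption) | 3.596 | 81.6% | 94.9% |
| 0.8 (assumption) | 2.877 | 57.1% | 82.0% |

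Only the first row is a target in the plan.

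**Coverage of the comparisons.**
- Seven outcomes as numbered: 7 × 0.007 = 0.049, within 5%.
- Eight, with either overt aspiration and pneumonia counted apart or the chi-square added: 8 × 0.007 = 0.056.
- Nine, with both: 9 × 0.007 = 0.063.

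These are Bonferroni upper bounds. Under independence the error is 1 − 0.993⁸ = 5.5% for eight and 1 − 0.993⁹ = 6.1% for nine. Under an assumed equal correlation r between normal test statistics, nine two-sided tests give 5.7% at r = 0.3, 4.9% at r = 0.5 and 4.3% at r = 0.6. Eight give 5.1%, 4.4% and 4.0%. Positive correlation is plausible, because several of these outcomes are read from the same DOSS scale.

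**The case against.** **The level was planned for.** The sample size was computed at 0.007, so the penalty was meant to be paid in patients. The gap between 93.0% and the stated 95% comes from 211 not following from the formula, not from the choice of level. This stands. A reader might infer that the primary analysis is invalid or badly underpowered. The documents do not support that: it is conservative, and about 93% power remains at the planned effect.

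**The flat correction buys something.** It lets each secondary outcome be claimed whether or not DOSS succeeds, and speed of recovery and aspiration are among the stated aims. This also stands, so it would be wrong to say that the stricter level brings no gain in error control. It brings none that the primary outcome needs.

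**The one-level figure.** It is tempting to take 1.0 as the plan's own target, because section 2.5.2 and the Discussion call a one-level DOSS improvement clinically significant. Those sentences describe change within a patient. The only between-group difference used for planning is 1.16.

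**The count.** A reader might infer that section 2.9 commits to nine confirmatory tests and so exceeds 5%. The text does not go that far. The correction refers to the number of outcomes, and seven are listed. The chi-square is called additional, and no test is named for pneumonia. The excess is therefore conditional, and small even if granted.

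**Conclusion.** The point holds as one of efficiency. DOSS is the only primary outcome and is tested at about one-seventh of the usual level, with no order of testing that would make this unnecessary. At the planned difference of 1.16 the cost is 93.0% against 98.6% power. This assumes 147.7 evaluable patients per arm, SD 2.39 and a normal comparison of two means; the actual analysis is by generalized estimating equations. The loss is larger if the true effect is smaller, but those figures rest on assumed effects.

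The coverage point is secondary. If the two aspiration endpoints and the chi-square are all confirmatory, the bound is 5.6% to 6.3% instead of 5%, and positive correlation may bring the actual error back to 5% or below. The two points share one cause, but dividing by eight or nine would settle only the second and would cost the primary still more power.

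**What to change.** Before any data are seen, and keeping 422 patients:

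1. Test DOSS alone at two-sided 0.05.
2. Only if it is significant, test a listed set of secondary comparisons with Holm at an overall 0.05: MSS, YPR-SRS, PAS, time to one-level improvement, time to oral intake, overt aspiration and aspiration pneumonia, each counted once. These are seven, so Holm's first step is 0.05/7 = 0.00714, no stricter than the present 0.007, and later steps are easier.
3. Name a test for aspiration pneumonia if it stays in that list.
4. Label the T1 oral-intake chi-square as supportive.
5. Restate the level and power in sections 2.7 and 2.9 to match: 98.6% at 211 per arm with 30% loss.

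The price is that no secondary claim can be made if DOSS fails. If independent secondary claims matter more, Holm over all listed comparisons, DOSS included, is the alternative. It is never less powerful than Bonferroni over the same list, though with eight entries its first step is 0.05/8 = 0.00625. Either way, the changed level is the stated basis of the sample size in an ethics-approved, registered protocol, so it should be made as a documented amendment. No extra patients or data are needed.
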